### Study population and clusters

Service users and clinicians comprise the study population in the cRCT, process and economic evaluation in the four European countries, which will be recruited from three clinical units (clusters) in each of the eight clinical sites and, thus, a total of 24 units (clusters). Due to differences in mental health care systems across the four European countries, clinical units (clusters) will vary in structure, service type, and size, which will enhance generalizability of findings and allow implementation to be examined under various conditions. Clinical units (as cluster and unit of randomization) will be community mental health teams (Scotland), tracks (Germany (at the Central Institute of Mental Health Mannheim (CIMH)), inpatient, outpatient and community-based services (Germany (at Psychiatric Centre Nordbaden), Belgium, and Slovak Republic). A clinical unit typically will comprise a multidisciplinary team (i.e., psychiatrists, psychologists, nurses, social workers, occupational therapists). In each of the eight clinical sites, 54 service users will be recruited from three clinical units (i.e., 18 service users per unit), and thus a total of 432 service users (*n*=288 in the experimental condition, *n* =144 in the control condition). In addition, around 100 clinicians of these service users from 24 clusters across all sites are estimated to be recruited in a period of 6 months (see Fig. 1). Recruitment and consent procedures as well as eligibility criteria are described in more detail in Supplementary Material 2.

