### Sample size calculation

We will test the primary hypothesis of the effect of the experimental vs. control condition (i.e., DMMH + additional implementation strategies + TAU vs. TAU) on service engagement as primary outcome (measured with the patient-reported SAQ total score as the dependent variable). We will use a fixed effects regression model controlling for unit effects, with a dummy variable for the condition (DMMH + additional implementation strategies + TAU vs. TAU), the SAQ engagement total score at baseline, and a dummy variable coding for the random allocation to ESM data collection at baseline. Ignoring in a first step the correlations between values taken from the same cluster, the total number of service users required to detect an effect of size d=0.4 (i.e., an effect size slightly lower than reported for service engagement in a previous study investigating the effects of an App-based mobile mental health solution [26]), with power 1- β = 0.80 at an alpha level of 0.05 with sample size ratio 2 (experimental condition) : 1 (control condition) is computed to be N0 = 201 for the null hypothesis that the difference between both experimental and control condition in terms of the mean SAQ score is zero at 2-month (t_1_) post-baseline, versus the alternative hypothesis that there is a difference (non-directional alternative). The statistical test will employ a fixed effects linear regression model with a variable representing treatment vs. control as the focal coefficient. The coefficient test will be performed at significance level α = 0.05, with the SAQ score at baseline as control variable and controlling for unit clustering. If all 24 units to be randomized have size n0 = (201/24=) 8.38 and assuming an intraclass coefficient of ICC = 0.05 [27], then N0 has to be increased to account for the effect of clustering by a factor of DEFF = 1+7.38×ICC = 1.37 for unit clustering. After appropriate upward rounding, this yields a total sample size of *N* = 288 service users, of whom 16 × 12 = 192 will be randomly assigned to the experimental condition (DMMH + additional implementation strategies + TAU) and 8 × 12 = 96 to the control condition (TAU). Further, based on previous research by IMMERSE partners and a meta-analysis investigating attrition in smartphone-based interventions [28], we expect an attrition of 35.5% from inclusion to 2-month post-baseline. For each of the eight clinical sites, this implies that a minimum of 54 service users will be recruited from three clusters (i.e., *n*=18 service users per cluster) and thus a total sample of 432 service users across all sites at baseline (i.e., with *n*= 16 × 18 = 288 in the experimental condition, *n* = 8 × 18 = 144 in the control condition), which allows for a 35.5% attrition rate to detect a medium effect size of d = 0.4 (with a power of 0.80, ICC=0.05, and α = 0.05). We will allow for an increase in recruitment target at all sites to up to *n*=108 per site (i.e., 36 service users per cluster) in order to compensate for delays in recruitment that may lead to overall under-recruitment across sites.

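### The design effect is computed at 8.38 service users per unit although 12 per unit are to be analysed, so 288 does not give the stated 80% power

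*Protocol article*

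**What the plan says.** All figures are in the protocol article, section Sample size calculation. The calculation first sets clustering aside. It gives "the total number of service users required to detect an effect of size d=0.4", "with power 1- β = 0.80 at an alpha level of 0.05", against a two-sided alternative ("versus the alternative hypothesis that there is a difference (non-directional alternative"), and reports the result as "sample size ratio 2 (experimental condition) : 1 (control condition) is computed to be N0 = 201".

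Clustering is then added. The 201 are divided over the 24 units to be randomized, giving 8.38 per unit, and with ICC = 0.05 the text concludes: "then N0 has to be increased to account for the effect of clustering by a factor of DEFF = 1+7.38×ICC = 1.37". After rounding up, the total is 288 analysed, of whom "16 × 12 = 192 will be randomly assigned to the experimental condition" and 8 × 12 = 96 to control. Allowing for 35.5% attrition, the plan recruits 18 per unit, 432 in all, and states that this design detects d = 0.4 with power 0.80 at ICC = 0.05. The design effect is not recomputed at 12 per unit.

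**The concern.** The design effect depends on how many people per unit are analysed. Multiplying an unclustered sample size by a design effect works when the unit size is set beforehand and the extra people come from extra units. Here the number of units is set at 24 and the extra people go into the same units. The inflation therefore raises the quantity that the design effect depends on, and a factor taken at 8.38 per unit is too small for units of 12.

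This calculation is the stated basis for the primary hypothesis on the SAQ total score at 2 months. If the power is lower than published, a reader will judge the trial's ability to detect d = 0.4 against a figure that its own inputs do not support. The estimand, the type I error rate and the analysis model are not affected.

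**Working it through.** **Inputs (Sample size calculation).** d = 0.4; two-sided alpha 0.05; power 0.80; allocation 2:1 (16 and 8 units); N0 = 201; 24 units; ICC = 0.05; analysed N = 288, or 12 per unit. The normal quantiles are 1.960 and 0.842, with sum 2.802.

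**Step 1: the plan's figure.** 201/24 = 8.38. DEFF = 1 + 7.38 × 0.05 = 1.369. 201 × 1.369 = 275.2, or 11.47 per unit, rounded up to 12. 24 × 12 = 288. The plan's figure reproduces exactly.

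**Step 2: design effect at the analysed size.** DEFF(12) = 1 + (12 − 1) × 0.05 = 1.55.
- Required by the plan's own rule: 201 × 1.55 = 311.6, against 288.
- Effective sample: 288/1.55 = 185.8, against 201.

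The rounding from 275 to 288 does not close the gap.

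**Step 3: power if N0 = 201 is accepted as giving 80%.** Power = Φ(√(185.8/201) × 2.802 − 1.960) = Φ(0.73) ≈ 0.77. Detectable d at 80% power = 0.4 × √(201/185.8) ≈ 0.416. This isolates the design-effect step.

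**Step 4: power computed directly at 2:1.** The noncentrality is 0.4 × √(185.8 × 2/9) = 2.57. Power = Φ(2.57 − 1.96) ≈ 0.73. With a t-test on 22 degrees of freedom (24 units − 2, an assumption) it is about 0.69.

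**Step 5: why steps 3 and 4 differ.** At 2:1 the unclustered total is 4.5 × (2.802/0.4)² ≈ 221, or 222 in whole 2:1 groups; exact regression and t-test calculations give 223 to 225. The stated 201 lies close to the 1:1 result (198 by normal approximation). The drop from 77% to 73% therefore comes from N0, not from the design effect.

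**Step 6: consistent unit size.** Solving 24m = N0 × [1 + (m − 1) × ICC] gives m = N0(1 − ICC)/(24 − N0 × ICC). For N0 = 201: 201 × 0.95/(24 − 10.05) = 190.95/13.95 = 13.7, so 14 per unit and N = 336. Check: DEFF(14) = 1.65, and 336/1.65 = 203.6, above 201.

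**Step 7: baseline correlation that would restore 80% at 288.** Adjustment scales the variance by 1 − r².
- On N0 = 201: r = √(1 − 185.8/201) ≈ 0.27, assuming that 201 already credits none.
- Computed directly: r = √(1 − 185.8/220.75) ≈ 0.40.

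The article states no such correlation.

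**The case against.** The step from 1.37 to 1.55 cannot be disputed on the stated inputs. Four things can be said about its weight.

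- **Size.** On the plan's own N0 the loss is about 3 percentage points. It would be wrong to charge the full fall to 73% to the design effect. This stands, and the two figures are kept apart above.
- **Baseline adjustment.** The primary model includes baseline SAQ, and a moderate correlation would recover the loss. True, but the calculation states no correlation and takes no explicit credit for one, so the published 80% does not rest on it.
- **More people or more units.** The plan allows up to 36 per unit, and Randomization and blinding allows additional units at each site. At 36 recruited and 35.5% attrition, 23.2 per unit would be analysed: DEFF 2.11, effective sample 264, power about 87% computed directly. Both options are offered only against low recruitment. They mitigate the problem but are not the design for which 80% is claimed.
- **Degrees of freedom.** The article names a t-test but gives no degrees of freedom, which may be set in the SAP. The 69% is therefore conditional.

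A reader might also infer that unequal unit sizes make matters worse, from the statement that "clinical units (clusters) will vary in structure, service type, and size". The documents do not show this. The sentence describes the units as services, the same section sets 18 service users for each unit, and the ceiling of 36 is raised at all sites alike. No coefficient of variation is given. Nor do the documents support power below 69% from degrees of freedom lost to site terms, because the primary model as described has no site term.

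**Conclusion.** The concern holds. For 24 equal units of 12 at ICC = 0.05, the design effect is 1.55 and the effective sample 186, against the 201 that the plan requires. The claim of power 0.80 at d = 0.4 is therefore wrong as written.

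Power for 288 analysed, before any credit for baseline adjustment, is about 77% if N0 = 201 is accepted and about 73% computed directly at 2:1 (about 69% if the test uses 22 cluster degrees of freedom). This rests on equal unit sizes, no additional units and the stated ICC. It does not show that the trial will be underpowered in practice: a baseline correlation of about 0.27 to 0.40 would bring 288 back to 80% by normal approximation. What is shown is that the published figure does not follow from the published inputs.

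**What to change.** Compute the design effect at the analysed unit size, using m = N0(1 − ICC)/(24 − N0 × ICC), and correct the text in one of two ways.

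1. **Keep 80% without baseline credit.** For N0 = 201 this needs 14 analysed per unit, 336 in all. At 35.5% attrition that is 14/0.645 = 21.7, so 22 recruited per unit and 528 in total, against 432 planned. The number rises further if N0 is itself corrected for 2:1.
2. **Keep 288.** Restate the power as about 73–77% before baseline adjustment, or state and justify the baseline to follow-up SAQ correlation relied on to reach 80% (about 0.27 on the plan's N0, about 0.40 computed directly).

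Under either option, label any allowance for unequal unit sizes as an assumption, and say which degrees of freedom the power figure uses.

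The second option costs a few restated numbers and no further participants. The downside is that the published power becomes less favourable, or comes to depend on a correlation that has to be defended.

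### With 432 recruited and 35.5% attrition about 279 are analysed, not 288, and at 11.6 per unit the stated inputs give power of about 0.76 or less, not 0.80

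*Protocol article*

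**What the plan says.** All the figures are in the Sample size calculation section of the protocol article.

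- The number of service users "required to detect an effect of size d=0.4", "with power 1- β = 0.80 at an alpha level of 0.05 with sample size ratio 2 (experimental condition) : 1 (control condition", two-sided, "is computed to be N0 = 201" before clustering is considered.
- The design effect takes its unit size from this number: "If all 24 units to be randomized have size n0 = (201/24=) 8.38". With ICC 0.05 the section obtains 1.37.
- After rounding up, the total is 288: 16 × 12 = 192 experimental and 8 × 12 = 96 control.
- On losses before the primary endpoint, "we expect an attrition of 35.5% from inclusion to 2-month post-baseline".
- At each site "a minimum of 54 service users will be recruited from three clusters", that is 18 per unit and 432 overall (288 + 144), "which allows for a 35.5% attrition rate to detect a medium effect size of d = 0.4". The same sentence attaches power 0.80, ICC 0.05 and alpha 0.05 to this claim.

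The Study population and clusters section repeats 18 per unit and 432. The section also allows up to 36 per unit, but ties this to delays in recruitment, not to attrition.

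**The concern.** The 288, the 35.5% and the 432 do not fit together as printed, since 432 less 35.5% is not 288. A reader cannot tell how many service users the primary analysis is expected to include, or which number the attrition allowance was meant to protect.

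The sentence also makes a claim that can be checked: 432 recruited with 35.5% lost gives power 0.80 at d = 0.4 and ICC 0.05. The design effect depends on how many are analysed per unit, and the one used belongs to a smaller unit than the trial will have at two months. If the claim fails, the power stated for the primary outcome is too high even when recruitment and attrition go exactly as planned.

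**Working it through.** **Inputs, all from the Sample size calculation section:** d = 0.4, two-sided alpha 0.05, power 0.80, allocation 2:1, N0 = 201, 24 units, ICC 0.05, attrition 35.5%, 18 recruited per unit. Power figures use the normal approximation with SD = 1.

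**1. Reproducing the plan's figures**
- Design effect: 1 + (8.38 − 1) × 0.05 = 1.37.
- Clustered requirement: 201 × 1.37 = 275.4, or 275.4/24 = 11.5 per unit. Rounded up this is 12 per unit, 288 in total.
- Attrition applied to the unrounded figure: 275.4/0.645 = 427, and 427/24 = 17.8 per unit. Rounded up this is 18 per unit, 432 in total, which matches.
- Attrition applied to 288: 288/0.645 = 446.5, or 18.6 per unit, which does not match 432.

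**2. Analysed number at the expected attrition**
- 432 × 0.645 = 278.6, or 18 × 0.645 = 11.61 per unit.
- Against the printed 288: 288 − 278.6 = 9.4 short. The loss that 432 tolerates is 1 − 288/432 = 33.3%.
- Against the unrounded requirement, rounded to 276: the tolerated loss is 1 − 276/432 = 36.1%.

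**3. Design effect at the analysed unit size**
- DEFF = 1 + (11.61 − 1) × 0.05 = 1.53.
- Effective N = 278.6/1.53 = 182, against 201 needed. Equivalently, 201 × 1.53 = 308 analysed are needed, against 279.

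**4. Power, accepting that an effective N of 201 gives 0.80**
- The standardised effect at 201 is 1.960 + 0.842 = 2.802.
- At 182 it is 2.802 × √(182/201) = 2.666, so power = Φ(2.666 − 1.960) = 0.76.

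**5. Power recomputed at 2:1 without baseline adjustment**
- The standardised effect is 0.4 × √(N × 2/9).
- At 182 it is 2.544, so power = Φ(0.584) = 0.72.
- At 201 the same formula gives 0.76, so N0 = 201 does not itself give 0.80 at 2:1. The formula needs (1.960 + 0.842)² × 4.5/0.16 = 221, or 222 in whole 2:1 triples.

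**6. Share due to the 288-to-279 gap**

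| Design effect | 288 analysed | 279 analysed |
|---|---|---|
| At actual unit size (1.55; 1.53) | 0.729 | 0.720 |
| Held at 1.37 | 0.781 | 0.767 |

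The gap costs about 1 point of power.

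**7. Baseline adjustment (assumed range)**

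The section states no correlation between baseline and two-month SAQ. Assume that a correlation r multiplies the residual variance by (1 − r²), that d = 0.4 is on the unadjusted SD, and that ICC 0.05 still applies after adjustment. The effective N is then 182/(1 − r²).

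| r (assumed) | Effective N | Power |
|---|---|---|
| 0 | 182 | 0.72 |
| 0.3 | 200 | 0.76 |
| 0.42 | 221 | 0.80 |
| 0.5 | 243 | 0.84 |

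**The case against.** The strongest defence is that 432 is not a mistake. The section's own N0 and design effect require 275.4, and 432 less 35.5% leaves 278.6, which is enough. On this route the 288 is only 275.4 rounded up to whole users per unit, and the shortfall of 9 uses up rounding slack. This stands.

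It rules out three stronger readings that a reader might infer:

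- That 18.6 per unit was rounded down to 18. The document does not say so, and rounding 17.8 up gives the same 18.
- That the true tolerance is 33.3%. This holds against the printed 288 but not against the section's unrounded requirement.
- That 19 per unit is the remedy. It would keep 288 (19 × 0.645 = 12.3 per unit, 294 analysed), but DEFF is then 1.56 and the effective N is 188, still below 201. Keeping N0 = 201 and solving the design effect consistently gives 201 × 0.95/(1 − 201 × 0.05/24) = 328.5 analysed, or 14 per unit rounded up. Then 14/0.645 = 21.7, so 22 recruited per unit.

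The defence does not rescue the power statement. The 275.4 is sufficient only if units have 8.38 members, and at 278.6 analysed they have 11.6.

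A second defence is that the primary model adjusts for baseline SAQ, which raises power. This is fair, and under the assumptions in step 7 a correlation of about 0.42 would restore 0.80. But the section states no correlation and does not claim this gain. It is also possible that 201 already contains some adjustment: an R² of about 0.10 would take 223 down to 201. In that case 0.76 is the relevant figure.

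Finally, 54 per site is a minimum, so more may be recruited. The claim of 0.80, however, is attached to 432.

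**Conclusion.** The concern holds in two parts of unequal weight.

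The smaller part is presentation. At the expected attrition about 279 are analysed, the section prints only 288, and it does not say which number the allowance refers to. Taken alone this costs about 1 point of power.

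The larger part is that the sentence claiming power 0.80 at 432 recruited, 35.5% attrition and ICC 0.05 is wrong on its own inputs. Power is about 0.76 if N0 = 201 is accepted, and about 0.72 if recomputed at 2:1 without baseline adjustment. The loss comes from the design effect and, in the second figure, also from N0. It does not come from the gap of 9.

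These values assume equal unit sizes, attrition spread evenly over units and arms, and a normal reference distribution. A baseline correlation, if one was assumed, would raise them. The documents do not show that the trial cannot reach 0.80, only that the stated inputs do not give it.

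**What to change.** In the Sample size calculation section:

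- State that 432 recruited with 35.5% attrition gives about 279 analysed (about 11.6 per unit), and that 288 is the clustered requirement rounded up to 12 per unit.
- Restate the power for 279 analysed, with the design effect at that unit size (1.53) and the 2:1 allocation.
- If the calculation relies on adjustment for baseline SAQ, state the assumed correlation and its basis, and show power over a plausible range.

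This is a correction of text and one recalculation. It changes neither the recruitment target nor the analysis. If the restated power is judged too low, whether to recruit more per unit is a separate decision. The existing ceiling of 36 per unit leaves room, but its stated purpose would have to be widened beyond recruitment delays.

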
### Statistical analysis

Statistical analysis will be performed according to the intention-to-treat principle based on a pre-registration and statistical analysis plan (SAP) published on the OSF [15]. Please see the published SAP [15] for further details on the statistical analysis. The primary hypothesis of the effect of condition (i.e., DMMH + additional implementation strategies + TAU vs. TAU) on service engagement as primary outcome (measured with the patient-rated SAQ total score as the dependent variable) will be tested using a fixed effects regression model controlling for unit effects, with a dummy variable for the condition (DMMH + additional implementation strategies + TAU vs. TAU), the SAQ engagement total score at baseline, and a dummy variable coding for the random allocation to ESM outcome data collection. The focal coefficient of the model is the coefficient for the dummy variable for condition, tested via t-test for the null hypothesis of no difference between the two conditions against the two-sided alternative hypothesis that there is a difference at 2-month post-baseline. The experimental condition will be interpreted as having a statistically significant effect in the hypothesised direction if the estimated coefficient indicates a higher SAQ score (i.e., more service engagement) for this condition and the associated t-test is significant at α < .05. The primary endpoint analysis will be based on observed data using Full Information Maximum Likelihood estimation for the linear regression model. As there is minimal missing data expected in baseline and structural variables in the statistical model for the primary endpoint, we will evaluate whether more robust approaches in sensitivity analyses will be needed and would report results based on multiple imputations (please see the SAP [15] for further details).

We will test the secondary hypotheses of the effect of condition (DMMH + additional implementation strategies + TAU vs. TAU) on personal recovery, self-management, shared-decision making, personal therapy goal attainment, social functioning, social participation, quality of life, and symptom improvement/severity as secondary outcomes using a mixed model (restricted maximum likelihood estimation). First, we will use α < 0.05 to indicate statistical significance, i.e., evidence against the null hypothesis of no difference between the two conditions across all three time points (an average difference between conditions across 2-month, 6-month and 12-month post-baseline) against the two-sided alternative hypothesis that there is a difference; second, we will use, for each secondary outcome, linear contrasts at each of the three follow-up time points to investigate whether there is a potential difference between the conditions (adjusted nominal level α/3 each). The covariates included in the model in addition to the condition indicator will be the respective secondary outcome score at baseline, time (as a three-level factor), the baseline × time interaction, the condition × time interaction, and a dummy variable coding for the random allocation to ESM data collection at baseline. In addition to p-values, 95% confidence intervals for the time-specific treatment effects will be calculated. Clustering of measures within clinical units (and of repeated measures within participants) will be taken into account by allowing residuals within clinical units (and participants) to be correlated with an unstructured variance-covariance matrix. As ESM data have a multilevel structure, multiple ESM observations (level 1) will be treated as nested within time points (i.e., 2-month, 6-month, and 12-month post-baseline) (level 2) and time points will be treated as nested within participants (level 3). Additional analyses will investigate between-site effects (via condition-site interactions) and associations with unit-level characteristics. Another set of additional analyses will investigate a potential ESM method effect on primary and secondary outcomes due to ESM outcome data collection alone (based on the within-trial randomisation of participation in ESM outcome data collection).

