To achieve our overarching aim, this study will:Establish, in a pragmatic cRCT of the DMMH and other implementation strategies to support its use in service users and clinicians in routine care settings, i) **R**each (i.e., service user participation), ii) **E**ffectiveness (defined as the interaction of efficacy and implementation in real-world settings), operationalized as greater service user engagement at 2-month post-baseline in the experimental than control condition as primary outcome, iii) **A**doption (i.e., proportion of service users and clinicians having used DMMH components in routine care), iv) **I**mplementation (defined as delivery of the DMMH as intended in routine care) and v) **M**aintenance (defined as the extent to which the DMMH becomes sustainable part of routine care at 6-month and 12-month post-baseline). Consistent with the **RE-AIM** framework [16], this will provide the basis for assessing the public health impact of implementation and scale-up of ESM-based monitoring, reporting and feedback via the DMMH and other implementation strategies. The primary hypothesis will be that, compared with the control condition (i.e., Treatment-As-Usual (TAU)), patient-reported service engagement, assessed with the total score of the Service Attachment Questionnaire (SAQ) at 2-month post-baseline (primary outcome), will be higher in the experimental condition (DMMH + additional implementation strategies + TAU), while controlling for service user engagement and clinical unit at baseline (please see our preregistration published on the Open Science Framework (OSF) [15] for further details on all hypotheses).Understand how service users leverage DMMH to support their health and well-being, and evaluate the process of implementing ESM-based monitoring, reporting and feedback in routine clinical care pathways using a realist evaluation framework [17] to identify in vivo configurations of contexts, processes and mechanisms of action, and how these are associated with outcomes of implementation in service users, clinicians, and managers/system administrators.Investigate the economic costs of the DMMH and other implementation strategies, and determine their cost-effectiveness and cost-utility vis à vis TAU.

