## Methods

### Study design

In this hybrid effectiveness-implementation study [14], a parallel-group, assessor-blind, multi-centre cRCT will be conducted, in which 24 clinical units (as the unit of randomization) at eight sites in four European countries are randomly allocated using an unbalanced 2:1 ratio to one of two conditions: (a) the experimental condition, in which participants receive the DMMH and other implementation strategies in addition to treatment as usual (TAU) or (b) the control condition, in which participants are provided with TAU. Outcome data in service users and clinicians will be collected by assessors masked to random allocation of clinical units at four time points: at baseline (t_0_), 2-month (t_1_), 6-month (t_2_) and 12-month post-baseline (t_3_). The cRCT will follow Consolidated Standards of Reporting Trials (CONSORT) reporting guidelines [18] and relevant extensions [19, 20]. Standard Protocol Items: Recommendations for Interventional Trials (SPIRIT) [21] and Template for Intervention Description and Replication (TIDiER) [22] checklists are available as Supplementary Materials 7 and 8. The primary outcome will be patient-reported service engagement assessed with the SAQ at 2-month post-baseline, a measure of service users’ experience of, and engagement with, their treatment and service [23]. The cRCT will be combined with a process and economic evaluation to provide in-depth insights into in-vivo context-mechanism-outcome configurations as well as economic costs of implementing the DMMH in routine care.

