### Randomization and blinding

A validated and concealed procedure for randomization will be applied independently of the research team using an unbalanced 2:1 ratio for allocating clinical units to the experimental and control condition stratified by the eight clinical sites without contamination (cross-exposure to the experimental condition). An unbalanced allocation ratio of 2:1 will be used to allow for more detailed investigation of implementation aspects and protect against attrition. This will include an option in the concealed randomization procedure to allocate additional clinical units at each of the eight clinical sites if recruitment rates are lower than expected for some clinical units.

After random allocation of clinical units, clinicians in the experimental condition will be informed about allocation status. This will be done through an independent researcher and not the outcome assessors, who will be blind to allocation status for assessments at baseline, 2-month, 6-month and 12-month post-baseline. Further, there will be an independent contact person, who will not be involved in any assessments, for any questions regarding the recruitment and assessment procedure by service users and clinicians. The trial cannot be fully “blind” because clinicians and service users cannot be masked towards the allocation of clinical units to the experimental or control condition. However, outcome assessors will be blinded to allocation status when assessing eligibility, baseline scores and outcomes at baseline, 2-month, 6-month and 12-month post-baseline. Any data specific to the experimental condition (e.g., on clinical feasibility) will be stored in a separate database. Any breaks in masking will be documented in the trial master file and another blinded assessor will be allocated to repeat the assessment and complete the next set of assessments where possible. To maintain the overall quality and legitimacy of the trial, code breaks will only be done in exceptional circumstances when knowledge of the treatment allocation is absolutely essential for further management of the service user.

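### The primary model combines clinical-unit fixed effects with a condition dummy that is constant within each unit, so as written the focal coefficient is not identifiable

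*Protocol article*

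**What the plan says.** All references are to the protocol article.

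- **Unit of randomisation.** Study design: "24 clinical units (as the unit of randomization) at eight sites in four European countries are randomly allocated using an unbalanced 2:1 ratio". Randomization and blinding describes "allocating clinical units to the experimental and control condition stratified by the eight clinical sites without contamination". With three units per site this gives 16 experimental and 8 control units.
- **Primary model.** Statistical analysis: the primary hypothesis "will be tested using a fixed effects regression model controlling for unit effects, with a dummy variable for the condition". The other listed terms are the baseline SAQ total and a dummy for random allocation to ESM outcome data collection. The condition coefficient is tested by a two-sided t-test in a linear regression fitted by full information maximum likelihood (FIML).
- **Same model again.** Sample size calculation: "We will use a fixed effects regression model controlling for unit effects, with a dummy variable for the condition". Later in that section the test is described once more as a fixed effects linear regression, "with the SAQ score at baseline as control variable and controlling for unit clustering".
- **Hypothesis.** Background states the primary hypothesis "while controlling for service user engagement and clinical unit at baseline".
- **Sample size.** The number of service users is inflated by a design effect with ICC 0.05.
- **Secondary outcomes.** These get a mixed model by restricted maximum likelihood (REML), with residuals allowed to correlate within clinical units. Neither feature is stated for the primary outcome.

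**The concern.** In a cluster randomised trial, condition varies only between units. Unit fixed effects absorb all between-unit variation, including the part that is due to condition. Nothing remains from which to estimate the condition effect, whatever the sample size or the ICC. FIML does not help, because it deals with missing values and not with aliased columns.

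The sample size section assumes a different error structure. A design effect is needed only if between-unit variance is part of the error of the condition effect, and unit fixed effects take that variance out.

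At stake is the test of the primary outcome. If the model stays as written, the analyst must depart from it once the aliasing appears. The way the fit is forced then decides what the coefficient means and whether the 5% level holds.

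**Working it through.** **Inputs from the protocol article:** 24 units (16 experimental, 8 control) in 8 sites; 288 analysed, so m = 12 per unit; ICC 0.05; d = 0.4 in SD units; two-sided α = 0.05; stated power 0.80. **Assumed:** an ICC range of 0.01 to 0.10 around the stated value, because no ICC after baseline adjustment is given.

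**1. The plan's own figures.** The design effect reproduces: 1 + 7.38 × 0.05 = 1.369, and 201 × 1.369 = 275.2, which rounds up to 24 × 12 = 288. The starting value of 201 does not reproduce under 2:1 allocation. The normal formula gives 74 controls and 222 in total, and the noncentral t gives 225; equal allocation gives 198 to 200. That is a separate matter and the present point does not depend on it.

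**2. Rank of the stated model.** The 24 unit columns have rank 24. Adding condition gives 25 columns, still of rank 24, because condition equals the sum of the 16 experimental unit columns. With baseline SAQ and the ESM dummy there are 27 columns of rank 26. If site effects replace unit effects, there are 11 columns of rank 11, so condition is then estimable.

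**3. What a forced fit gives.**

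- *Condition is the column dropped:* there is no estimate.
- *One unit column is dropped per arm:* the condition coefficient compares two single units. Its SD is √(2 × (0.05 + 0.95/12)) = √0.2583 = 0.51. In a between-unit analysis it is √((0.05 + 0.95/12) × (1/16 + 1/8)) = √0.02422 = 0.156. Simulated type I error is 12.4% and power at d = 0.4 is 0.22.
- *Unit effects are constrained to sum to zero within arm:* the arm contrast is estimable, but its standard error uses within-unit variance only. The true variance exceeds the variance used by the ratio R = 1 + m × ICC/(1 − ICC), and type I error is 2 × (1 − Φ(1.96/√R)).

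| ICC | R (m = 12) | Type I error, formula | Type I error, simulated |
|---|---|---|---|
| 0.01 (assumed) | 1.12 | 6.4% | 6.5% |
| 0.05 (stated) | 1.63 | 12.5% | 12.3% |
| 0.10 (assumed) | 2.33 | 19.9% | 20.4% |

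The simulations used 4,000 trials per setting, 24 units of 12, total SD 1, no site effect, and a baseline score independent of outcome.

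**4. Tests against between-unit error.** In the same simulations at ICC 0.05, type I error was 5.0% for a comparison of unit means (24 − 2 = 22 df) and 4.9% with site strata (24 − 8 − 1 = 15 df).

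**5. Power of a valid test.** The noncentrality is 0.4/0.156 = 2.57. Power is 0.69 with 22 df and 0.67 with 15 df, without credit for baseline adjustment. For ICC 0.01 to 0.10 it runs from 0.83 to 0.56 (22 df) and from 0.81 to 0.54 (15 df).

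**The case against.** The strongest reply is that unit indicators are inferred. The article names only two dummies, condition and ESM allocation; unit enters as something controlled for. The sample size section also speaks of controlling for unit clustering and applies a design effect. Both would fit a regression with fixed covariates and clustering handled separately, for instance by a cluster-robust variance. The article refers to a published SAP, where the variance estimator and degrees of freedom would normally be found.

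Part of this stands. The looser reading is possible, and the absence of a variance estimator or degrees of freedom from the article is no finding. But the article does more than stay silent. It gives the model as fixed effects with unit effects in two sections, and it keeps the mixed model and within-unit correlation for secondary outcomes. A reader who follows the text would fit the aliased model.

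Four stronger readings are tempting and not supported:

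- *Software would drop a column unnoticed.* The documents say nothing on this, an aliased term is normally reported as omitted, and a missing condition estimate would be seen.
- *The trial's type I error is 12%.* That figure belongs to particular forced fits at ICC 0.05. The protocol describes none of them.
- *This is the only confirmatory test.* The article also tests secondary hypotheses at 0.05. It is the primary test.
- *Clinical unit must be struck from the primary hypothesis.* A random unit intercept also controls for unit, so a clarification is enough.

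**Conclusion.** The primary model is wrong as written. With unit fixed effects the condition coefficient cannot be identified. This follows from the design alone and rests on no assumption about ICC, sample size or attrition. It also contradicts the error structure behind the article's own design effect.

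The size of the harm depends on how a fit is forced. With unit effects constrained within arm, type I error is about 12.5% at ICC 0.05 and 12 per unit, and about 6% to 20% over the assumed ICC range. These figures take no account of any change in ICC after baseline adjustment.

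A reader might infer that the trial will be analysed invalidly. The documents do not show that: the SAP is not at hand, and the reference to unit clustering may mean something sound. If the SAP does specify a valid model, the article contradicts it and still needs correcting. Nor is the whole shortfall from 0.80 to 0.67–0.69 due to the model, since separate sample size issues contribute.

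**What to change.** In Statistical analysis and Sample size calculation, replace unit fixed effects with an analysis that tests condition against between-unit variation. Either of these would do:

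- a linear mixed model with a random intercept for clinical unit, for example by REML with Kenward-Roger or Satterthwaite degrees of freedom; or
- a unit-level analysis of covariate-adjusted unit means.

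In either case, account for condition, baseline SAQ, ESM allocation and site (the randomisation stratum) as fixed effects, and use small-sample degrees of freedom, about 15 to 22. Align the FIML wording with the chosen model. In Background, clarify that clinical unit is controlled for as a random effect or cluster. Settle this before the locked data are released, and bring the SAP into line.

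The change needs wording and no extra data, but it has a price. Standard errors will be wider than those from a within-unit error term. Before credit for baseline adjustment, power is about 0.67 to 0.69 at d = 0.4, ICC 0.05 and 288 analysed. The stated 0.80 should therefore be recalculated for the chosen model, with any gain from baseline adjustment stated as an explicit assumption.
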